### Study objectives and endpoints

The primary objective of this trial is to show that after TAPP repair for unilateral and bilateral inguinal hernias the acute postoperative pain caused by mesh fixation with tissue glue is less than with staple fixation.

The primary efficacy endpoint of the TISTA trial is pain under physical stress at 24 h after surgery. Pain will be rated by the patient using a numeric rating scale (NRS). The NRS ranges from 0 to 10 in steps of one, with 0 representing no pain at all and 10 the worst imaginable pain. The NRS is comparable to the visual analogue scale (VAS) where the degree of pain is marked on a 10 cm long line. In practical terms, average NRS and VAS scores (in cm) can be considered equivalent. The patient is first asked to rate the pain at rest and then to rate it after physical stress. Physical stress is induced by a 90° bending of the hip joint on the operated side(s). The secondary endpoints of the trial and their definitions are summarized in Table 
1.

**Table 1 T1:** Secondary endpoints and definitions

**Secondary endpoints**	**Definitions**
Pain rated before surgery and at 4, 8, 12, 36, 48 h after surgery	Measured on a numeric rating scale from 0-10 at rest and upon bending the hip joint on the operated side
Operating time	Time, in minutes, from the first skin incision to the application of dressing
Length of hospital stay	Time, in days (with one decimal precision), from start of surgery to hospital release
Postoperative analgesic requirements	Amount (g/day) and type (paracetamol, metamizole, morphine) of analgesic required after surgery, before hospital discharge
Incidence of persistent pain (neuralgia)	Neuralgia defined as:
	• The presence of intermittent hyperesthesia, burning sensation, or jabbing pain in the ipsilateral, inguinal area nerves (genitofemoral nerve, lateral cutaneous femoral nerve, ilioinguinal and iliohypogastric nerve) [20,22,27]
	• Evaluation will be performed 14 days, 1, 3 and 12 months after surgery
	• The degree of pain will measured as described above
Postoperative morbidity	Categorized according to Dindo et al [28], and it includes:
	• Wound infection, defined as infections treated without further surgery and identified by clinical examination without microbiological confirmation
	• Hematoma or seroma formation, identified by clinical examination alone, before discharge from hospital, which does not require radiological confirmation

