	• Re-operation, defined as the need for re-operation during the initial hospital stay
	• Bleeding
	• Urinary retention, urinary tract infection
	• Pulmonary infection
	• Any serious deviation from the normal postoperative course
Time to return to normal activities	Time, in days, from hospital discharge to first working day
Relapse	Within 1 year of surgery
Economic impact	Calculated based on the following factors:
	• Cost for glue, staples, and instruments to apply glue or staples
	• If relevant: cost for excess operating time for the “slower” mesh fixation
	• Length of hospital stay (cost/day)
	• Medical leave of absence (converted into a monetary amount based on an average salary)

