### Sample size calculation

The sample size was calculated under the hypothesis that either glue fixation or staple fixation is superior for the primary endpoint (= pain after 24 h)(two-sided analysis). Lovisetto reported a mean VAS pain score of 1.9 for glue fixation and 2.6 for staple fixation one month after TAPP repair
[19]. The observed difference of 0.7 is usually considered to be of no clinical relevance. We thus assumed a difference of 1 as a clinically relevant difference. Standard deviation was estimated to be equal 1, resulting in a standardized effect size of 1 which generally is considered clinically relevant. The sample size calculation was performed as two-sided analysis with a type I error of α = 0.05 and a power of (1-β) = 0.90.

Based on these assumptions, we calculated that 23 patients per arm would be required for unilateral hernias (t-test for two independent samples with common variance). Assuming a drop-out rate of 20%, the total number of patients needed per arm is 29, resulting in a total of 58 patients with unilateral hernias. For the second arm with bilateral hernias we calculated that 19 patients would be required (t-test for paired samples), assuming an intra-individual correlation of 0.2 (derived from a preliminary, unpublished analysis of patients with bilateral inguinal hernias that had undergone a Lichtenstein procedure). With a drop-out rate of 20%, a total of 24 patients with bilateral hernias would be required, resulting in a total of 82 patients for the entire study.

With an annual case load of approximately 100 in the previous years, we estimate that patient recruitment should be achieved within one or two years.

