### Statistical analysis

The statistical analysis will be performed with SPSS Statistics for Windows (IBM Corp., Armornk, NY, USA). A two-sided p-value <0.05 will be considered statistically significant. Descriptive statistics will be used to analyze the baseline characteristics. For the superiority analysis of pain intensity at 24 h after surgery, the Mann−Whitney U and Wilcoxon tests will be applied, as appropriate. To adjust for multiple testing, the Hochberg procedure will be applied
[29].

Pain measurements performed at 4, 8, 12, 24, 36, 48 h after surgery by patients with unilateral and bilateral hernias will be analyzed in one mixed model to assess the mean ranks of the NRS scores with adjustments for time, treatment, and unilateral versus bilateral hernias. To compare other continuous secondary endpoints (e.g., operating time, length of hospital stay, postoperative administered analgesics, time to return to normal activity, and economic impact), the Mann−Whitney U and Wilcoxon tests will be applied, as appropriate. Chi-square statistics will be used to compare categorical secondary endpoints (e.g., incidence of chronic pain, rate of recurrence, and postoperative morbidity). Auxiliary, non-confirmatory analyses will be performed to assess the influences of baseline patient characteristics and treatment characteristics on the primary and secondary outcomes.

Intermittent missing values will be replaced by linear interpolation (e.g. post-operative pain values within 48 h after surgery). No interim analysis is planned for this study. Data from patients withdrawn from the study will be disregarded, unless exclusion is based on a postoperative patient request, and the patient agrees to the use of existing documented data.

The confirmatory analysis will be performed based on an intention-to-treat (ITT) design, and it will adhere to ITT principles. When a protocol violation occurs, a per protocol analysis (PP) will be performed for comparison.

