## Discussion

This study was designed as a randomized trial with a two-by-two, parallel design. We aimed to compare patients with unilateral hernias that received mesh implants, fixed with either tissue glue or staples and to evaluate patients with bilateral hernias that received mesh implants fixed with tissue glue on one side and staples on the other side. In the latter group, the same patient will rate the pain associated with both methods; these ratings will not be influenced by inter-individual biases present in the unilateral hernia arm. To further reduce biases, both patients and observers (staff evaluating the pain) will be blinded to the assigned treatment.

We expect that mesh implants fixed with tissue glue will be associated with less postoperative pain, shorter hospital stay, and a shorter sick leave after the operation compared to implants fixed with staples. In addition to enhancing patient comfort, the tissue glue fixation will also have an economic impact, by reducing health care costs. Because we can evaluate both inter-individual and intra-individual biases in pain perception, this study will provide important insights for future studies that aim to investigate pain. This study will therefore provide novel information that is currently lacking in the literature.

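### Return to normal activities is timed from hospital discharge, itself an outcome that fixation may change, so any difference in stay shifts this secondary endpoint against the arm discharged earlier

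*Protocol article*

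**What the plan says.** All references are to the protocol article.

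- **Study objectives and endpoints, Table 1, time to return to normal activities:** "Time, in days, from hospital discharge to first working day".
- **Same table, length of hospital stay:** "Time, in days (with one decimal precision), from start of surgery to hospital release". The end of this interval is the start of the one above.
- **Statistical analysis:** the continuous secondary endpoints compared by Mann-Whitney U or Wilcoxon tests include "operating time, length of hospital stay, postoperative administered analgesics, time to return to normal activity, and economic impact". Stay and return to activity are thus tested as separate endpoints.
- **Discussion:** the authors expect glue to give "less postoperative pain, shorter hospital stay, and a shorter sick leave after the operation compared to implants fixed with staples".

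No section counts the return-to-activity endpoint from surgery or adjusts it for length of stay.

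**The concern.** A randomised comparison of a duration needs a starting point that treatment cannot move. Discharge is not such a point. It follows allocation, it closes an interval that the trial analyses as an outcome, and the Discussion predicts that fixation will change it. If that prediction is right, the two arms are timed from systematically different points in recovery.

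A true gain in time from surgery to work could then be reduced, erased or reversed in this endpoint. The test could also favour staples when the two arms return to work equally soon after surgery.

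**Working it through.** **1. The plan's own figure.** The only computed figure is the sample size for the primary endpoint. The inputs, from Sample size calculation, are "two-sided analysis with a type I error of α = 0.05 and a power of (1-β) = 0.90", "We thus assumed a difference of 1 as a clinically relevant difference" and "Standard deviation was estimated to be equal 1".

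- Two-sample t-test (noncentral t), difference 1, SD 1: 23 per arm, power 0.912. This agrees with "23 patients per arm would be required for unilateral hernias".
- Paired t-test, correlation 0.2: SD of differences = √(2 × (1 − 0.2)) = 1.265, giving 19 patients, power 0.903.
- Drop-out of 20%: 23 / 0.8 = 28.75, so 29 per arm and 58 in all; 19 / 0.8 = 23.75, so 24. Total 58 + 24 = 82.

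The figures reproduce. None of them concerns return to activities, which has no power calculation.

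**2. The identity.** For each patient let S be the time from surgery to the first working day, L the length of stay, and R the Table 1 endpoint. Then

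R = S − L.

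Taking mean differences, glue minus staples:

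D(R) = D(S) + (mean L in staples − mean L in glue).

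A stay saving of d days with glue therefore adds d days to glue's result, relative to counting from surgery. This needs no outside figure.

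**3. Numerical illustration.** The documents give no expected stay or time to work. Assume stays of 3 days (staples) and 2 days (glue), with staples patients back at work on day 14 after surgery.

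| Glue back at work on day | Difference from surgery (glue − staples) | Difference from discharge (glue − staples) |
|---|---|---|
| 14 | 0 | (14 − 2) − (14 − 3) = +1 |
| 13.5 | −0.5 | 11.5 − 11 = +0.5 |
| 13 | −1 | 11 − 11 = 0 |
| 12 | −2 | 10 − 11 = −1 |

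The third row is the case where the return date moves forward by exactly the stay saved. Nothing counts against glue there, but the one-day gain does not appear.

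**4. Effect on the rank test, illustration only.** The simulation used 23 patients per unilateral arm, a two-sided Mann-Whitney test at 0.05 and 4,000 trials per scenario. Assumed, not from the documents: surgery-to-work mean 14 days, SD 3 days; stay mean 2.5 days, independent of the return date.

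| Stay saved by glue | Return to work earlier with glue, from surgery | Significant for glue, from surgery | Significant for glue, from discharge |
|---|---|---|---|
| 0 d | 2 d | 57% | 53% |
| 0.5 d | 2 d | 57% | 35% |
| 1 d | 2 d | 57% | 17% |

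With 1 day saved and no difference in return date, the discharge-based test favours staples in 17% of trials; with 0.5 day saved, in about 8%. The nominal rate in that direction is 2.5%. With no difference in stay, the two definitions perform almost alike.

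**5. Who is affected.** Under Trial interventions, each bilateral patient receives both fixations. Return to work is one value per patient, so this group offers no glue-versus-staples contrast on it. The issue is confined to the unilateral arms.

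**The case against.** The strongest defence is that Table 1 splits recovery into two adjoining intervals, surgery to release and release to work, and compares both. A hospital day saved is credited under length of stay and again as a daily cost under economic impact. On this view the endpoint is narrow rather than wrong, and misleads only someone who reads it as total recovery time. It stands that the information is not lost. But the endpoint is labelled as time to return to normal activities, which invites that reading, and two separate rank tests on the parts do not test their sum.

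The defence also notes that care after surgery is standardised, so stays may hardly differ. That is possible, and the documents give no figure to settle it. The authors nevertheless state that they expect a shorter stay with glue.

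Three stronger readings are tempting but not supported:

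- A reader might infer that every day of stay saved is necessarily held against glue. That is true only for a given date of return to work. If the return date moves forward equally, the gain is omitted, not reversed.
- A reader might infer that sick leave after the operation goes unmeasured. Table 1 lists leave from work as a separate cost item under economic impact. Its starting point is not stated, so the documents do not show that it is missed.
- A reader might infer that the endpoint will in fact mislead. Without a stated difference in stay, that remains a possibility.

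**Conclusion.** The point holds as a conditional one. The time origin is a post-randomisation event that the authors expect treatment to shift, and any resulting difference in mean stay enters the endpoint one for one against the arm discharged earlier, relative to counting from surgery. That offset is algebra.

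Its actual size is unknown. At zero difference in stay there is no bias, and the 0.5- and 1-day cases and all the simulated percentages rest on assumed values. The scope is the unilateral comparison of one unpowered secondary endpoint. The primary endpoint, its analysis and the 82 patients are unaffected. It is worth correcting because the remedy is cheap, not because it threatens the trial's main conclusion.

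**What to change.** In Table 1, define time to return to normal activities as the number of days from surgery to the first working day, the same origin as length of stay. Test that between the unilateral arms, and report discharge-to-work as a descriptive component only. Methods for reducing bias places randomisation during surgery, so the start of surgery precedes allocation and cannot be moved by it.

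No additional data or patients are needed: start of surgery is already required for length of stay, and the first working day for the present endpoint. The cost is a documented amendment to a prespecified secondary endpoint. Trial status reports recruitment as ongoing and Statistical analysis plans no interim look, so the change should be dated and recorded before the analysis.

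### Table 1 charges operating time to the cost endpoint only as the excess of whichever fixation proves slower, and only 'if relevant', so the trial's own data decide who is charged and whether

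*Protocol article*

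**What the plan says.** In the protocol article, Table 1 (Study objectives and endpoints) lists economic impact as a secondary endpoint, "Calculated based on the following factors": device costs, operating time, hospital stay and medical leave.

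- Device costs are "Cost for glue, staples, and instruments to apply glue or staples". Stay is priced per day and leave at an average salary. None of these three carries a condition.
- Operating time enters only as "If relevant: cost for excess operating time for the “slower” mesh fixation".
- The same table defines operating time as a secondary endpoint in its own right: "Time, in minutes, from the first skin incision to the application of dressing". It is thus one figure per operation.

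The Statistical analysis section names "postoperative administered analgesics, time to return to normal activity, and economic impact" among the continuous secondary endpoints to be compared by Mann-Whitney U or Wilcoxon tests, with a two-sided p below 0.05 counted as significant.

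**The concern.** A rank test needs a cost for each patient, defined in the same way in both arms. The operating-time item is worded at the level of the fixation method. Someone must first see which method took longer, then decide whether the excess is relevant, then charge it to that method. Both the charged arm and the on/off switch are results of the trial, and the article gives no criterion for the switch.

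Two things are at stake. The endpoint's definition can change after the operating times are known. And if an estimated arm difference enters the patient scores as though it were a known price, the test ignores the uncertainty of that estimate.

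**Working it through.** **Inputs from the article (Sample size calculation).** The planned numbers reproduce. A two-sample t-test with difference 1, SD 1 and two-sided alpha 0.05 has power 0.8997 at 22 per arm and 0.912 at 23, hence 23; 23/0.8 = 28.75, hence 29. For the paired test the SD of the difference is √(2(1 − 0.2)) = 1.265; power is 0.885 at 18 and 0.903 at 19, hence 19; 19/0.8 = 23.75, hence 24. The total is 2 × 29 + 24 = 82. The check below uses 23 and 29 per unilateral arm.

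**Inputs not in the article.** It gives no unit costs and no SDs for time or cost. Let r be the SD of operating-time cost divided by the SD of all other costs; r is assumed, from 0.05 to 2.

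**Effect on the estimate.** Let D be the observed arm difference in mean operating-time cost, glue minus staples. Adding max(D, 0) to every glue patient and max(−D, 0) to every staple patient shifts the mean cost difference by max(D, 0) − max(−D, 0) = D. Charging each patient's own minutes also shifts it by D. The estimated mean difference is the same.

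**Effect on the test.** With n per arm, other-cost SD σ, and time independent of other costs, the mean difference has variance (2σ²/n)(1 + r²). A constant adds nothing to the within-arm spread, so the test works with about 2σ²/n. The approximate type I error is 2[1 − Φ(1.96/√(1 + r²))]:

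- r = 0.2: 1.96/1.020 = 1.922, giving 0.055
- r = 0.5: 1.96/1.118 = 1.753, giving 0.080
- r = 1: 1.96/1.414 = 1.386, giving 0.166

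**Simulation.** Two-sided Mann-Whitney test at 0.05, no true difference in any component, normal costs, 20,000 runs (Monte Carlo standard error √(0.05 × 0.95/20,000) ≈ 0.0015). Each cell gives 23 / 29 per arm.

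| r | Arm difference as fixed charge | Fixed charge only if the operating-time test is significant | Each patient's own minutes |
|---|---|---|---|
| 0.1 | 0.048 / 0.049 | 0.047 / 0.051 | 0.046 / 0.048 |
| 0.2 | 0.048 / 0.052 | 0.048 / 0.052 | 0.046 / 0.049 |
| 0.3 | 0.060 / 0.059 | 0.050 / 0.048 | 0.047 / 0.047 |
| 0.5 | 0.070 / 0.074 | 0.057 / 0.053 | 0.044 / 0.048 |
| 1 | 0.152 / 0.157 | 0.071 / 0.073 | 0.043 / 0.050 |

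**Sensitivity of the fixed charge at r = 0.5.**

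- Log-normal other costs: 0.134 (23 per arm) and 0.143 (29 per arm).
- Correlation between time and other costs (29 per arm, normal): −0.3 gives 0.042, so no inflation; +0.3 gives 0.105.

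Charging each patient's own minutes stays between 0.043 and 0.052 in every normal and log-normal setting tried, for r from 0.05 to 2.

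**Bilateral patients.** They receive glue on one side and staples on the other in one operation (Trial interventions). Time from incision to dressing is a single figure, so neither an excess nor a patient's own minutes can be assigned to one fixation.

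**The case against.** The strongest reply is that the fixed charge is a reading, not the article's text. Table 1 lists factors; it does not say that the excess is a difference in arm means or that it is added to each patient. How the factors combine may properly be left to the full protocol or analysis plan, which is not shown. That stands: the missing unit costs and combination formula are no finding here, and the error rates above are conditional. It does not answer the rule that the article does state, which names the slower fixation as the one charged and makes the charge depend on an undefined relevance.

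The size also rests on r. If stay and salary-based leave dominate the cost variance, r is small and the inflation negligible. That stands too.

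The simulated null may be thought remote, since device costs differ by arm by design and would be equal only by coincidence. This is fair as to exact equality in every component. The omitted variance is nevertheless a property of the scoring and makes the stated precision too high whatever the true difference.

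A reader might infer more than the documents support:

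- *That the cost test is anticonservative without qualification.* It depends on how the excess is allotted, on r, and on the correlation between time and other costs.
- *That false positives always fall on the arm slower by chance.* With the fixed charge and 23 per arm, about 69% of rejections do so at r = 0.25, 83% at r = 0.5 and 95% at r = 1.
- *That the estimated cost difference is biased.* Under the fixed charge it equals the difference obtained from each patient's own minutes. Setting one charged patient beside one uncharged patient says nothing about the arm comparison.

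**Conclusion.** The point holds as a minor correction. As written, the operating-time part of a formally tested endpoint is settled by the trial's own data, both in which arm is charged and in whether it is charged.

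The effect on the test is conditional. If the observed arm difference is added as a constant, with normal costs, time independent of other costs and 23 to 29 per arm, type I error is about 5% for r up to 0.2, 7% at r = 0.5 and 15% at r = 1. It is larger with skewed costs or a positive correlation, smaller if the charge is gated by a significance test, and absent at r = 0.5 with a correlation of −0.3. The article does not give r, so no single figure can be claimed. Only one secondary endpoint is concerned; the primary pain analysis and the sample size are unaffected.

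**What to change.** Replace the operating-time bullet in Table 1 with: operating-room cost = each patient's recorded operating time in minutes × a prespecified cost per minute, for all patients in both unilateral arms. Delete the words 'If relevant' and 'slower'. Fix the cost per minute before operating times are seen by treatment group.

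State that this patient-level cost comparison is restricted to the unilateral cohort. Including bilateral patients would require fixation time to be recorded separately for each side.

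The cost is a change of wording and one unit price. Operating time is already collected for every patient as a secondary endpoint, so the unilateral comparison needs no new data and no change to the sample size.

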### Standardization of treatments

Patient intra- and peri-operative care will be standardized and maintained identical for each patient, except for the mesh fixation technique. The patients will receive combined neuraxial and general anesthesia.

